### Open-label non-randomised study

The open-label study will go ahead if the treatment is found to be effective without safety concerns by the National Institute of Health Research (NIHR) and the National Health Service (NHS) England. MissionEB is not an adequately powered study for feasibility reasons, and as such, the judgement on the efficacy of UC-MSCs will be based on the totality of evidence from all clinical (primary and secondary) outcomes. The criteria for starting the open-label trial are based on the absence of any SUSARs which the DMEC consider to be of clinical concern. In addition, as this is a naturally progressive disease, the study will continue if there is an improvement in any of the primary or secondary outcomes for participants (improvement in disease severity, pain and itch and quality of life). The DMEC and Trial Steering Committee (TSC) will review and consider whether the data indicate evidence of improvement. Participants of the crossover trial will be invited to the open-label study and be given six infusions in total (two infusions at four monthly intervals, at day 0, month 4 and month 8) and followed up at month 12 and outcome measures taken at each visit. No placebo will be administered in the open-label study.

### Recruitment

The trial will be conducted at two sites in England, GOSH and Birmingham Children’s Hospital, which both specialise in paediatric dermatology and are nationally commissioned centres for paediatric EB. Informed consent will be taken by appropriately trained staff as per Section 5.5 of the full protocol.

### Participant eligibility

#### Inclusion criteria

Patients who have a diagnosis of RDEB characterised by partial or complete C7 deficiency, including generalised severe and generalised intermediate subtypes.Patients who are over 6 months and before their 16th birthday at time of consent. (Participants must be recruited before their 16th birthday to the crossover trial as this will allow for completion of the whole trial (crossover and open-label) before they are 18 and transition to adult services. However, if there are delays to the study due to dose de-escalation, all participants should be allowed the opportunity to partake in the open-label.)Patients whose responsible parent/guardian has voluntarily signed and dated an Informed Consent Form prior to the first study intervention. Whenever the minor child is able to give consent, the minor’s assent will be obtained in addition to the signed consent of the minor’s legal guardian.

#### Exclusion criteria

Patients with other subtypes of EB such as EB simplex, dominant DEB, junctional EB and Kindler EB.Subjects who have received oral or topical corticosteroids for more than seven consecutive days within 30 days of enrolment into this study, with the exception of the following steroids with non-systemic effects and intended to relieve oesophageal symptoms: oral viscous budesonide and inhaled fluticasone.Patients with a known allergy to any of the constituents of the investigational product.Patients with signs of active infection that requires treatment with oral or intravenous antibiotics within 7 days of screening.Patients with a medical history or evidence of active malignancy, including cutaneous squamous cell carcinoma.Patients with both (a) positive C7 ELISA and (b) a positive indirect immunofluorescence with binding to the base of salt split skin at screening.Patients who are pregnant or of childbearing potential who are not abstinent or practising an acceptable means of contraception, as determined by the investigator, for the duration of the treatment phase.Patients having received MSCs from any source in the last 9 months.Simultaneous or previous participation in any interventional trial within 3 months before entering this trial but participation in simultaneous registry and diagnostic trials during the trial is allowed.

### Randomisation and blinding

During both the internal phase I dose de-escalation trial and the main crossover trial, the allocation sequence will be generated by the randomisation statistician using a validated web-based randomisation system within the Sheffield Clinical Trials Research Unit (CTRU). Site research staff blind to the treatment allocation will enter their details on the randomisation system. The randomisation email will be received by the pharmacy and the UC-MSC manufacturer (INmuneBio), who will make up the participant treatment as instructed (either placebo or active treatment) and label this with the participant identifier.

For the internal dose de-escalation trial, participants will be randomised in four cohorts and the choice of the cohort block depends on toxicity decisions made by the DMEC after each cohort (figure 1). The first nine participants are divided into two cohorts, all allocated using simple randomisation: the first four participants will be randomised (3:1) to receive (UC-MSCs:placebo) and the second five participants will be randomised (3:2) to receive (UC-MSCs:placebo). This gives an overall allocation (6:3) for these nine participants to receive (UC-MSCs:placebo). It should be noted that treatments stated here are technically for the first period of the crossover trial. These participants will only receive their second period treatments of the crossover if no concerning toxicity issues are found.

For the main crossover trial, participants will be randomised (to achieve 1:1 overall allocation) to either receive UC-MSCs (in period 1) followed by a placebo (in period 2) or placebo (in period 1) followed by UC-MSCs (in period 2) using simple blocked randomisation. Only the randomisation statistician will have access to the block size during the trial. Participants who have already received period 1 and 2 treatments on the correct UC-MSCs dose during the internal dose de-escalation trial will not be re-randomised again in the main crossover trial as they have contributed valid data for both periods. However, in the event that the dose needs to be de-escalated, participants who previously took part in the dose de-escalation study on a higher dose will washout for at least 9 months and be re-randomised to take part in the main crossover trial using the new, lower dose.

This is a double-blinded study, so all participants and the research team will be unaware of the treatment allocation. Intended unblinding will only occur after the crossover trial during the extended open-label study.

### Intervention and placebo control

#### Internal phase I dose de-escalation trial

The investigational medicinal product (IMP) is a suspension of allogenic UC-MSCs, in a solution containing Dulbecco’s phosphate buffer saline, ZENALB (a solution of human albumin serum) and dimethyl sulfoxide. The placebo consists of the same solution, minus the allogenic UC-MSCs. The full composition of the IMP and placebo is described in Section 6.1 of the full protocol. Each participant will receive two intravenous infusions (days 0 and 14), administered as a slow bolus. At the start, participants within a cohort will receive 2–3×10^6^ cells/kg (or placebo). If dose de-escalation is triggered based on observed toxicity (figure 1), then participants in subsequent cohorts will receive 1–1.5×10^6^ cells/kg (or placebo).

#### Main crossover trial

Each participant will receive a total of four intravenous infusions. Treatment period 1 infusions are administered on days 0 and 14 (either UC-MSC or placebo, depending on the randomised allocation). For the treatment period 2 participants, crossover treatment and the infusions are administered at month 9 and 2 weeks later, administered as a slow bolus over 10 min. The rationale for treatment dosing and washout periods is described in Section 2.2.1 of the full protocol. If it is not necessary to de-escalate the dose following phase I, participants will receive 2–3×10^6^ cells/kg. If a dose de-escalation is required, dosing schedules will be reduced as outlined in figure 1.

#### Open-label study

Each study participant will receive a total of six intravenous infusions (days 0 and 14, month 4 and 2 weeks later, month 8 and 2 weeks later). If it is not necessary to de-escalate the dose following phase I, participants will receive 2–3×10^6^ cells/kg; otherwise, dosing schedules will be reduced as outlined in figure 1.

### Aims and objectives

The overall aim of this study is to assess whether repeated infusions of UC-MSCs are safe and can benefit children with RDEB.

### Primary outcomes

#### Internal phase I dose de-escalation trial

Toxicity as defined by a participant experiencing a SUSAR within 48 hours of a participant receiving an infusion.

#### Main crossover trial

The primary outcome will be change in disease severity as measured by the Epidermolysis Bullosa Disease Activity and Scarring Index (EBDASI) at 3 months post-infusion of UC-MSCs (from day 0, where day 0 is the treatment period baseline).

#### Open-label non-randomised study

The primary outcome will be the same as for the main crossover trial but assessed at 4, 8 and 12 months from day 0 of the open-label study.

MissionEB is not an adequately powered study for feasibility reasons, and as such, the judgement on the efficacy of UC-MSCs will be based on the totality of evidence from all clinical (primary and secondary) outcomes.

### Secondary outcomes

The secondary outcomes applicable for the internal phase I dose de-escalation and crossover parts of the study are:

Change in EBDASI total score at 6 months post-infusion (from day 0, period baseline).Change in disease severity measured by iscorEB at 3 and 6 months post-infusion (from day 0, period baseline).^18^Change in general clinical appearance of skin disease as assessed by clinical photography at 3 and 6 months post-infusion (from day 0, period baseline).Change in pain and itch as assessed by the Wong–Baker FACES Pain scale for children over 6 years old^19^ and Leuven itch scale scores^20^ at 3 and 6 months post-infusion (from day 0, period baseline).Additionally, for pain and itch, changes in the amount of analgesia and itch medications required will be assessed. Participants or their guardians will be asked to detail what pain and itch medication the participant has taken in the last 48 hours, including dose and frequency. At 3 months post-infusion, clinicians blinded to treatment allocation will compare whether this is unchanged, increased or decreased since baseline (day 0, period baseline).Change in quality of life according to validated Child Health Utility 9D (CHU-9D) scoring system (16) at 3 and 6 months post-infusion. Quality-of-life assessment will be conducted using CHU-9D. The CHU-9D is a sensitive and validated nine-item child health-related quality-of-life assessment scale developed specifically with and for children and will be used in children aged 7 years and over. An age appropriate by proxy version will be used for children aged 3–6.A health economic analysis to assess the costs and consequences of treatment with UC-MSCs versus usual care.Adverse events (AEs) and serious adverse events (SAEs) both during the trial and long-term AEs after the trial.Safety bloods (routine blood tests and C7 antibodies).Research bloods (will be stored for further analysis following a separate research application).Serum for cytokines, interleukin (IL)-10, IL-13, IL-22, tumour necrosis factor-alpha at screening, day 0, day 14, month 9 and 2 weeks later in the crossover trial and all visits for the open-label study, except the final 12-month visit.

The outcomes above are also applicable for the open-label for months 4, 8 and 12.

### Safety monitoring and AE reporting

All AEs and adverse reactions will be recorded. SAEs will be subject to expedited reporting requirements. Hospitalisations that are expected to take place as a result of disease progression will not be subject to these reporting requirements. Definitions of AEs and adverse reactions, and a list of exempt events are detailed in Section 9 of the full protocol.

### Trial oversight

The TSC and the DMEC consist of independent members (experts in the field and patient representatives) who will monitor trial data and progress and oversee the trial implementation on behalf of the funder and sponsor. The day-to-day running of the trial is coordinated by the Trial Management Group (TMG), which consists of grant co-applicants and CTRU representatives.

### Sample size

RDEB is a rare condition, and the sample size of 36 (for the crossover trial) is based on feasibility, including availability of the patients and not formal power considerations. As such, the statistical analysis focuses on estimation rather than hypothesis testing. Table 1 gives the standardised widths for the precision of the trial (for a continuous outcome) as assessed by the half-width of a 95% CI.

**Table 1 T1:** Standardised widths for the precision of the trial

Completed	Precision
36	0.49
30	0.53
25	0.59

The sample sizes for safety gatekeeping during the internal dose de-escalation phase are based on a 4+5 design, which is a variant of a 3+3 design with controls to allow seamless transition into the main crossover trial. The open-label follow-on study will depend on available participants for whom further treatment is deemed appropriate following the crossover trial.

### Statistical analysis

#### Internal dose de-escalation phase

The objective of this phase is to monitor the safety of the proposed dose based on the assessment of toxicity data that relates to all SUSARs due to study treatment as deemed by the study clinicians. These data will be assessed by the DMEC, who will recommend whether to continue with the proposed dose, halve the proposed dose to the main crossover trial or stop the trial if the proposed dose is deemed unsafe.

#### Crossover trial

The main crossover trial will be reported according to the Consolidated Standards of Reporting Trials extension for reporting randomised crossover trials.^21^ The primary analysis will be based on the intention-to-treat principle that will include participants with outcome data on two periods of the crossover design.

The study is not formally powered, and estimation rather than formal hypothesis testing is the primary aim of the analysis, although p values may be provided when frequentist statistical models are fitted.

The primary outcome is the change in disease severity as measured by the change in EBDASI total score (across all five domains) at 3 months from day 0.^22^ This outcome will be analysed using a linear mixed-effects model that will include treatment, period and baseline (for each period, if necessary) in the model with a random effect on the participant. The difference in means (mean difference) with 95% CIs giving a range of plausible effects will be estimated using restricted maximum likelihood methods and Satterthwaite df.

To aid interpretation and ability to make probabilistic statements about the distribution of the treatment effect, an equivalent Bayesian linear mixed-effects model will be fitted using non-informative priors on model parameters. This will allow us to estimate the probabilities of the mean difference (treatment effect) being within a certain interval of potential interest to clinicians. For example, the probability of UC-MSCs causing any improvement in disease severity. The analysis of the primary outcome at 3 months and all secondary continuous outcomes will be analysed similarly. In case of missing data, the missing data mechanism will be explored, and multiple imputation may be applied as a sensitivity analysis as appropriate (where necessary).

Other sensitivity analyses will be performed to evaluate the robustness of the primary analyses. The statistical analysis plan will detail methods, including handling of endpoints measured across multiple domains.

There will be no interim analyses during the crossover trial and open-label follow-on study. However, safety data, including toxicities, will be monitored continuously by the DMEC throughout the trial.

It should be noted that judgements on the efficacy of UC-MSCs will be based on the totality of evidence from both primary and secondary clinical outcomes.

#### Open-label follow-on study

We plan to undertake no formal statistical analyses of the 12-month open-label data. This follow-on phase does not have a control group, so no formal comparisons will be made. As a result, the outcomes assessed during the 12-month continued treatment open-label study will be analysed descriptively based on available data. The objective is to assess whether the efficacy observed in the crossover phase (if any) is maintained over these 12 months.

### Qualitative study

We will aim to interview at least 10 participant and parent pairs (approximately five from each site and from both arms) at the 3-month and 12-month visit during the trial to gather their views on their symptoms following treatment and the impact on their lives. This information will add value to the quantitative data and help commissioners to contextualise the findings. We will seek TSC patient and public involvement input in developing the interview questions and methods used in the interviews. The TMG will be involved with the topic guide development, and a research assistant/qualitative researcher will undertake the interviews. Interviews will be conducted by a blinded researcher, with children aged 6 and over, and we will interview parents of all age groups where possible. We will aim to interview the children and parents separately while maintaining comfort for the child and parent.

### Health economics

We do not expect the intervention to lead to any reduction in the cost of care over the study period. This is due to the fact the children will stay on their medication and will continue to have to attend reviews and investigations, and will continue with their current skin care. Even if the skin and wounds improve, the way they will be dressed is unlikely to change as often the dressings are used for protection. As such, we will not collect resource use data on current treatments, and the cost analysis will focus on the costs associated with the infusion of UC-MSCs.

Health benefits will be measured using the CHU-9D, with quality-adjusted life-years compared over the randomised interval.

Mathematical modelling, including external evidence, will be used to explore the potential longer-term health benefits and costs associated with UC-MSCs (eg, long-term reductions in costs of bandages and dressings, avoidance of skin cancer). This analysis will be exploratory.

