Assess the safety of repeated UC-MSCs in children with RDEB.Assess the efficacy of repeated UC-MSCs in improving quality of life and symptoms (eg, pain, itch) in children with RDEB.Undertake a health economic analysis to assess the costs and consequences of treatment with UC-MSCs versus usual care.Explore patients’ and parents’ views in relation to treatment effectiveness and acceptability.

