**Figure 2 F2:**
[figure not shown]
Overview of the phase I, crossover and open-label study timelines. EBDASI, Epidermolysis Bullosa Disease Activity and Scarring Index; MSCs, mesenchymal stem cells; QoL, quality of life.

Outcomes will be measured at 0, 3, 6, 9, 12 and 15 months. All children will be followed up every 3 months as part of their clinical care for the first year following the first infusion. A cost consequence analysis will also be undertaken.

We will explore the impact of the treatment on participants by conducting interviews with children and parents (n=10 dyads or individuals) in both arms at the 3-month and 12-month follow-up timepoints.

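### The cost analysis counts infusion costs only, on a one-sided assumption about usual care that the trial's own medication and safety outcomes could test

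*Protocol article*

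**What the plan says.** The secondary objectives in the Introduction include an economic one: "Undertake a health economic analysis to assess the costs and consequences of treatment with UC-MSCs versus usual care". The Secondary outcomes section repeats it as an outcome, and the Main crossover trial section names the method: "A cost consequence analysis will also be undertaken".

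The Health economics section then sets the scope. Resource use on current treatments will not be collected, and "the cost analysis will focus on the costs associated with the infusion of UC-MSCs". The reasons given are that no fall in the cost of care is foreseen within the study, that "the children will stay on their medication", that reviews, investigations and skin care go on as before, and that dressings serve largely as protection and so will probably not change. Longer-term savings are left to an exploratory model with external evidence.

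Elsewhere, the Secondary outcomes section states that "changes in the amount of analgesia and itch medications required will be assessed". Families report pain and itch medication over a 48-hour recall, with doses and frequencies. At 3 months blinded clinicians judge whether use has risen, fallen or stayed the same since the period baseline. Adverse events and serious adverse events are also secondary outcomes, and the section on safety monitoring and AE reporting has all adverse events and reactions recorded.

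**The concern.** The article treats medication as constant when it sets the costs and as an open question when it sets the outcomes. If UC-MSCs reduce pain and itch, less analgesia and itch medication is one of the effects the trial is set up to detect. The cost side rules that effect out in advance.

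The argument also runs in one direction. It explains why costs should not fall and says nothing about why they should not rise. A cell infusion can cause reactions that need treatment or admission. Those events are recorded, but the article does not say that the care for them is costed.

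The final report goes to the funder, and the Qualitative study section has commissioners in view as readers. They would see a cost difference labelled as UC-MSCs against usual care that almost nothing observed in the trial could have changed.

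**Working it through.** The article states no cost, unit price or event rate, so there is no figure to reproduce. The check is to write out the cost difference and see which parts trial data can move.

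**Decomposition.** For one treatment period, UC-MSCs minus usual care:

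ΔC = ΔC(infusion) + ΔC(pain and itch medication) + ΔC(adverse-event care) + ΔC(other care)

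**What the article does with each part:**

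| Part | Treatment in Health economics | Does the trial record it? |
|---|---|---|
| Infusion | Costed | Yes, two infusions per period |
| Pain and itch medication | Taken as unchanged, so 0 | Yes, 48-hour recall with dose and frequency; direction of change judged at 3 months |
| Adverse-event care | Not mentioned | Events yes; care costs not stated |
| Reviews, investigations, skin care, dressings | Taken as unchanged, so 0 | No resource use collected |

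**Result as planned.** Let c be the cost of one UC-MSC infusion, and assume that usual care involves no infusion. Then ΔC = 2c + 0 + 0 + 0 = 2c, with adverse-event care at 0 unless it is classed as an infusion cost. No value of the medication outcome changes this.

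**What is missed.** Let m be the true difference in medication cost per period and a the true difference in the cost of adverse-event care. The planned figure is then off by m + a, or (m + a)/(2c) as a fraction. The sign of m is open, because the outcome allows for a rise or a fall. The article's reasoning does not exclude a > 0. None of c, m and a is given, so the error has no numerical value here.

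**How good the recorded data are.** Three months is about 365/4 = 91 days, so one 48-hour recall at month 3 covers 2/91 = 2.2% of them. Costing medication over a period therefore needs extrapolation and belongs in a sensitivity analysis. Hospital admissions expected from disease progression are exempt from expedited reporting, so admissions taken from serious adverse event reports may be incomplete.

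**The case against.** Leaving out costs that are the same under both treatments is a recognised choice in an incremental analysis, and the article gives reasons for expecting them to be the same. The reasons on reviews, skin care and protective dressings are plausible, and nothing else in the article contradicts them. That part stands.

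A cost-consequence analysis can also report medication change and adverse events as consequences without pricing them. This is true, and it means the information is not lost to the reader. It does not repair the cost figure, nor does it reconcile the premise of unchanged medication with an outcome that measures whether it changes.

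Care for infusion reactions might fall within costs associated with the infusion. The wording allows that reading but does not state it. Later adverse events and admissions would fit it less naturally.

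Finally, the recorded data are thin for costing. This is right, and it is why the proposal is a supplement to the base case and not a replacement for it.

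**Conclusion.** The point holds in a limited form. The cost difference against usual care is largely set by assumption. One component of that assumption is itself a trial outcome, and another, adverse-event care, is not addressed. The size in money cannot be derived from the article. This is a secondary analysis, and the primary outcome and its analysis are not affected.

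Three stronger readings are tempting, and the article does not support them.

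- **That the economic objective cannot be met.** This goes too far. If the omitted costs really are equal, infusion cost is the right incremental cost.
- **That QALYs will be compared over 9 months in period 1 and 6 months in period 2.** The visits run from 0 to 9 and from 9 to 15 months, and "quality-adjusted life-years compared over the randomised interval" leaves the interval undefined. But no section plans a 9-against-6 comparison, and CHU-9D change is set at 3 and 6 months after infusion. Even with whole periods and an assumed utility of 0.7, the gap of 0.7 × 3/12 = 0.175 QALY enters the two sequences with opposite signs. The period-adjusted contrast is (0.175 − 0.175)/2 = 0. Without adjustment it is also 0 at 18:18. Only an unadjusted contrast with unequal sequences leaves a bias, such as (20 − 16) × 0.175/36 = 0.019 at an illustrative 20:16. The article aims for 1:1 overall and puts period in its model for continuous outcomes; it does not name QALYs there.
- **That the CHU-9D change from proxy to self-report at age 7 biases the comparison.** Children turning 7 fall in both sequences alike, so the change is at most added noise. The rule for such children is a detail that the full protocol may give.

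**What to change.** In the Health economics section:

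1. Keep infusion cost as the base case.
2. Add the cost, by treatment period, of care for recorded adverse reactions and serious adverse events, including admissions.
3. Add a sensitivity analysis that costs the recorded 48-hour pain and itch medication, and state the extrapolation used.
4. Remove or qualify the premise that medication is unchanged, so that it agrees with the Secondary outcomes section.

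As a clarification only, name months 0 to 6 of each period as the QALY window.

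The cost is a little analysis work, mainly on data already recorded. The added figures will be approximate, because medication is a 48-hour snapshot and admissions expected from disease progression may not be fully captured. Both limits should be reported with the results.
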